**Other Supplementary Materials for this manuscript include the following:**

Final protocol

SAP

Materials and Methods

Collection and Storage of Samples for Proteomics Assays:

Prior to the start of the first cycle of chemotherapy and at the end of treatment, peripheral blood samples of consented patients were taken for proteomics assays. Standard operational protocols were followed when collecting plasma samples. In a nutshell, peripheral blood samples (2 mL per person) were collected in an EDTA anticoagulant tube and centrifuged for 15 minutes at 1,000 g/min. The Plasma was immediately transferred to a clean polypropylene test tube and stored at -80°C after centrifugation.

Extraction, Digestion, and Fractionation of Protein

The cellular debris from the plasma sample was removed by centrifugation at 12,000 g for 10 minutes at 4 °C. The supernatant was then transferred to a fresh centrifuge tube. PierceTM Top 14 Abundant Protein Depletion Spin Columns Kit was used to remove the top 14 high abundance proteins (ThermoFisher Scientific). The protein concentration was measured using a BCA kit as directed by the manufacturer.

The protein solution was reduced with 5 mM dithiothreitol for 30 minutes at 56 °C before being alkylated with 11 mM iodoacetamide for 15 minutes at room temperature in the dark. After that, the protein sample was diluted by adding 100 mM TEAB to a urea concentration of less than 2 M. Finally, trypsin was added at a trypsin-to-protein mass ratio of 1:50 for the first overnight digestion and a trypsin-to-protein mass ratio of 1:100 for the second 4 h digestion. The peptides were then desalted using a C18 SPE column.

Using an Agilent 300 Extend C18 column (5 m particles, 4.6 mm ID, 250 mm length), the sample was separated into fractions by high pH reverse-phase HPLC. The wavelength was 214 nm, and the temperature in the column oven was 35°C. After 30 minutes of washing with 95 percent equilibration buffer A, the peptide sample was fed into HPLC after the baseline was flat. Peptides were separated using a gradient of 2% to 60% acetonitrile in 10 mM ammonium bicarbonate pH 10 and collected at 1 minute in each tube. The 11th to 46th tubes were collected, and 36 tubes were mixed into 9 fractions and vacuum centrifuged to dry.

LC-MS/MS Analysis

The peptides were dissolved in liquid chromatography's mobile phase A and separated using the EASY-nLC 1200 ultra-high performance liquid phase system (ThermoFisher Scientific). Mobile phase A was an aqueous solution with 0.1 percent formic acid and 2% acetonitrile, while mobile phase B was an aqueous solution with 0.1 percent formic acid and 90% acetonitrile. The setting for liquid phase gradient: 0-114 minutes, 4 percent 33 percent phase B; 114-117 minutes, 33 percent 80 percent phase B; 117-120 minutes, 80 percent phase B. The flow rate was kept constant at 500 nL/min. The peptides were separated using an ultra-high performance liquid system, then injected into an NSI ion source for ionization before being evaluated in Q ExactiveTM HF-X (ThermoFisher Scientific).

The liquid phase parameters remained unchanged from when the library was created. Peptides were isolated using an ultrahigh performance liquid chromatography system and evaluated using Q ExactiveTM HF-X mass spectrometry. The high-resolution Orbitrap was used to detect and analyze peptide precursor ions and their secondary fragments. The primary mass spectrometer's scanning range was set at 385-1200 m/z, and the scanning resolution was set to 120000; the secondary scanning resolution was set to 15000. The data acquisition mode employed the data-independent scanning (DIA) program, in which peptide ions were fragmented in the HCD collision cell utilizing 27 percent of the fragmentation energy, followed by secondary mass spectrometry analysis. The secondary spectrum's automatic gain control (AGC) was set to 5E5, and the fixed initial mass was set to 200 m/z.

Protein Annotation in LC-MS/MS

MaxQuant search engine (v.1.6.15.0) was used to process the generated MS/MS data. Tandem mass spectra were compared to the human SwissProt database (20422 entries), which was concatenated with the reverse decoy database. Trypsin/P was chosen as the cleavage enzyme, with up to two missed cleavages permitted. In the first search, the mass tolerance for precursor ions was set to 20 ppm and 5 ppm in the main search, while the mass tolerance for fragment ions was set to 0.02 Da. FDR was adjusted to < 1%.

Proteomics Assays Data Analysis

Data on protein expressions came from two distinct groups (Group A: The FOLFOX4-ATRA group and Group B: the FOLFOX4-placebo group). Samples from the baseline (before treatment) and time point (after treatment) measurements formed 4 experimental subgroups (Subgroup A – before, Subgroup A – after, Subgroup B – before, Subgroup B – after). Samples from patients with PD, SD, PR, and CR were measured for each subgroup.

All protein expression values were normalized by calculating the relative abundance of each protein in each sample. Analyses of differential protein expression were conducted by fitting linear mixed models (LMM) with the lme4 R package25 and proteins whose expression levels were undetectable in more than 40 samples were not analysed The protein expression was a response variable (y), while the explanatory variables were treatment response (PD, SD, PR, and CR), time point (pre and post treatment), and treatment group (Group A and Group B) used as fixed effects. The patient ID was used as a random effect to allow us to account for the samples being paired (same samples measured in the pre and post therapy). To test for differences between different treatment responders to FOLFOX4-ATRA therapy, the generalized linear hypothesis (glht) function from the multcomp R package26 was utilized to test for the following three contrasts: (1) differences in protein expressions between patients with PD, SD, PR, and CR before therapy in Group A, (2) similar differences in Group B, and (3) any interaction when comparing differences between Group A and Group B. To test for the differences in the pre and post FOLFOX4-ATRA therapy, the following three contrasts were absotested: (1) differences in protein expressions in pre and post therapy in Group A, (2) differences in pre and post therapy in Group B, and (3) any interaction when comparing the differences between Groups A and B. The resulting p-values were adjusted using the FDR method to account for multiple comparisons.

Figure. S1.

[figure not shown]

Typical patient 1: A, C: Pulmonary metastasis before treatment; B, D: The lesions disappeared after FOLFOX4-ATRA

Figure. S2.

[figure not shown]

Typical patient 1: A, C: Abdominal metastasis before treatment; B, D: The lesions disappeared after FOLFOX4-ATRA.

Figure. S3.

[figure not shown]

Proteins that differed significantly between FOLFOX4-ATRA responders and non-responders prior to treatment (P value < 0.05). **A,** Heat map of significantly distinct proteins illustrating the difference between group A and group B patients for two-way comparisons between PD, SD, PR, CR, and RE (CR+PR), as well as the change in their differential expression in the pre and post therapy. The color of the heat map represents the regression coefficient in the linear regression test. **B,** the enrichment of Gene Ontology for different protein modules. **C,** The enrichment of KEGG pathways for different protein modules.

**CR_up:** SOD3, SERPINF2, AZGP1, APOF, PTPRM, FCN3, ALB, CACNA2D1, BTD, KRT81, TTR, SSC5D, PI16, GP5, IGKV1D−33. **RE_down**: FABP1, IGLV5−39, KRT6C, IGKV2D−29, IGLV5−45, ATXN7L2, VCAN, SLC4A1, PLGLA, IGLC7, MEGF8, FCGR3A, LRRC4. **PR_up**: F8, GSS, IGHV1−69, IGHV5−10−1, C4A, RNASE4, FBLN5, ALDOB, ANXA3. **SD_down**: UMOD, ABI3BP, AFM, ERAP2, IGHV3−38, IGLV2−18, TGFB1, ADARB1, IGLV7−46, WRAP73, IGLV3−19, ICAM3, IGLV1−51, F12, PSAP, PFN1, MST1L, IGLL5, IGKV3−20, IGHV3−7, IGHG2, FCGR3B, ATRN, DBH. **SD_up**: APCS, SPARCL1, PRG4, CFHR2, IGF2R, ASGR2, ITIH3, RELN, IGHD, ITIH4, ORM1, SERPINA3, SAA4, HPD, AGT, F11.

Figure. S4.

[figure not shown]

Proteins that differed significantly between pre and post FOLFOX4-ATRA treatment (P value < 0.05). A, Heat map of significantly distinct proteins illustrating the difference between group A and group B patients for two-way comparisons between PD, SD, PR, CR, and RE (CR+PR), as well as the change in their differential expression in the pre and post therapy. The color of the heat map represents the regression coefficient in the linear regression test. B, the enrichment of Gene Ontology for different protein modules. C, The enrichment of KEGG pathways for different protein modules.

**Treat_RE_up:** TPI1, CILP, IGHG3, TMEM198, A1BG, SELENBP1, CFHR4, PROCR, VCAM1, FCGR2A, LYVE1, APOC1, KNG1, MEGF8. **Treat_RE_down:** FLNA, IGHV2−70D, F8, IGF1, F12. **Treat_SD_up:** PLTP, ALCAM, ADGRG6, PLA2G7, COL18A1, OLFM1, FUCA1, F7, COL3A1, CDH2, APOC4, CD163, SPP2, ATRN, B4GAT1. **Treat_SD_down:** APCS, SAA4, HPD, C6, C8A, F9, ITIH4. **Treat_PD_up:** SLC4A1, PLS1, PFN1, PDIA3, IGLV1−51, IGKV3D−20, ATXN7L2, HBG2.

Table S1.

Univariate and Multivariable Analysis of OS

| Variables |  | | Univariate Analysis | |  | | Multivariable Analysis | |
| --- | --- | --- | --- | --- | --- | --- | --- | --- |
|  | p | HR | 95%CI | | p | HR | 95%CI | |
| Folfox-placebo | 0.027 | 1.792 | 1.068 | 3.005 | 0.037 | 1.740 | 1.033 | 2.931 |
| Sex | 0.033 | 2.005 | 1.056 | 3.807 | 0.158 | 1.612 | 0.830 | 3.129 |
| Age | 0.060 | 1.644 | 0.980 | 2.758 |  |  |  |  |
| PVTT | 0.191 | 1.429 | 0.836 | 2.440 |  |  |  |  |
| T stage | 0.013 | 1.207 | 1.040 | 1.401 | 0.035 | 1.178 | 1.012 | 1.371 |
| N stage | 0.964 | 0.979 | 0.391 | 2.451 |  |  |  |  |
| Number of metastasis>3 | 0.180 | 1.439 | 0.837 | 2.582 |  |  |  |  |
| Pulmonary metastasis | 0.234 | 0.701 | 0.390 | 1.259 |  |  |  |  |
| Metastatic organs>2 | 0.843 | 0.889 | 0.277 | 2.850 |  |  |  |  |
| HBV-DNA load | 0.332 | 1.361 | 0.731 | 2.533 |  |  |  |  |
| AFP>400 | 0.149 | 1.376 | 0.874 | 2.441 |  |  |  |  |
| TB>17.1 | 0.461 | 1.232 | 0.708 | 2.144 |  |  |  |  |
| ALT>44 | 0.740 | 0.891 | 0.450 | 1.763 |  |  |  |  |
| AST>44 | 0.717 | 1.114 | 0.621 | 2.000 |  |  |  |  |
| WBC>4 | 0.850 | 0.948 | 0.544 | 1.652 |  |  |  |  |
| PLT>100 | 0.302 | 1.361 | 0.758 | 2.443 |  |  |  |  |
| ALBI | 0.420 | 1.225 | 0.748 | 2.008 |  |  |  |  |
| Targeted therapy and /or Immunotherapy beore | 0.629 | 0.851 | 0.441 | 1.640 |  |  |  |  |

Table S2.

Univariate and Multivariable Analysis of DFS

| Variables |  | | Univariate Analysis | | |  | | Multivariable Analysis | | |
| --- | --- | --- | --- | --- | --- | --- | --- | --- | --- | --- |
|  | p | HR | | 95%CI | | p | HR | | 95%CI | |
| Folfox-placebo | 0.027 | 1.579 | | 1.053 | 2.368 | 0.037 | 1.541 | | 1.026 | 2.315 |
| Sex | 0.130 | 1.541 | | 0.881 | 2.696 |  |  | |  |  |
| Age | 0.162 | 1.333 | | 0.891 | 1.996 |  |  | |  |  |
| PVTT | 0.036 | 1.586 | | 1.031 | 2.441 | 0.833 | 0.925 | | 0.446 | 1.917 |
| T stage | 0.008 | 1.175 | | 1.044 | 1.324 | 0.093 | 1.187 | | 0.971 | 1.452 |
| N stage | 0.917 | 1.037 | | 0.521 | 2.067 |  |  | |  |  |
| Number of metastasis>3 | 0.100 | 1.442 | | 0.932 | 2.230 |  |  | |  |  |
| Pulmonary metastasis | 0.620 | 0.882 | | 0.539 | 1.446 |  |  | |  |  |
| Metastatic organs>2 | 0.883 | 0.939 | | 0.409 | 2.157 |  |  | |  |  |
| HBV-DNA load | 0.480 | 1.181 | | 0.744 | 1.874 |  |  | |  |  |
| AFP>400 | 0.073 | 1.448 | | 0.966 | 2.170 |  |  | |  |  |
| TB>17.1 | 0.814 | 1.057 | | 0.669 | 1.669 |  |  | |  |  |
| ALT>44 | 0.419 | 0.796 | | 0.457 | 1.385 |  |  | |  |  |
| AST>44 | 0.445 | 1.195 | | 0.756 | 1.889 |  |  | |  |  |
| WBC>4 | 0.079 | 0.678 | | 0.440 | 1.046 |  |  | |  |  |
| PLT>100 | 0.850 | 1.004 | | 0.671 | 1.622 |  |  | |  |  |
| ALBI | 0.527 | 1.130 | | 0.773 | 1.653 |  |  | |  |  |
| Targeted therapy and /or Immunotherapy beore | 0.549 | 1.155 | | 0.721 | 1.851 |  |  | |  |  |

Final protocol

**Combined FOLFOX4 with All-Trans Retinoic Acid versus FOLFOX4 with placebo in treatment of Advanced Hepatocellular Carcinoma with Extrahepatic Metastasis: A randomized, double blind comparative study (“ATFOX” study)**

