# Study Design

This is a multicenter, double-blinded, placebo-controlled, randomized clinical trial in advanced HCC patients with extrahepatic metastasis. Subjects will be randomly assigned to one of the two arms, either ATRA+FOLFOX or FOLFOX alone. Our study has been registered at <http://www.chictr.org.cn> (ID: ChiCTR-IIR-17012916).

**
[figure not shown]
**

After screening for eligibility and signing of informed consent, qualified subjects will be randomized in a 1:1 ratio to receive ATRA+FOLFOX4 (Group A) or Placebo + FOLFOX4 (Group B). Randomization will be stratified by site and treatment assignments will remain blinded throughout the study.

Names of Therapeutic Agents:

- All-trans-Retinoic Acid (ATRA)
- Oxaliplatin (OXA)
- 5-Fluorouracil (5FU)
- Leucovorin (LV)

Mode of Administration:

ATRA+FOLFOX4 (Group A): ATRA 20 mg oral 3 times/day for 3 days prior to the initiation of chemo (FOLFOX4). ATRA will be discontinued at the end of FOLFOX4(OXA 85mg/m2 iv day1, LV 200mg/m2 iv day1 and day 2, 5FU 400mg/m2 iv bolus at hour 2 and then 600 mg/m2 iv over 22 hours on day 1 and day 2, once every 2 weeks) and a total of 6 cycles were performed. Placebo+FOLFOX4 (Group B):The placebo (replacing ATRA) will be given orally 3 times/day for 3 days prior to the chemo. The placebo will then be discontinued at the end of FOLFOX4 and a total of 6 cycles were performed. The follow-up phase began once a patient terminated the treatment phase.

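### The first proteomics sample is timed by chemotherapy, not by the first ATRA or placebo dose, so the rule permits a Group A baseline drawn after up to 3 days of ATRA

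*Combined protocol and SAP*

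**What the plan says.** The supplementary Materials and Methods (Collection and Storage of Samples for Proteomics Assays) give one rule for the timing of plasma: "Prior to the start of the first cycle of chemotherapy and at the end of treatment, peripheral blood samples of consented patients were taken". The rule sets a latest time for the first draw, namely the first chemotherapy cycle. It does not mention the first dose of ATRA or placebo.

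The protocol (Study Design, Mode of Administration) starts Group A on "ATRA 20 mg oral 3 times/day for 3 days prior to the initiation of chemo (FOLFOX4"). For Group B it states: "The placebo (replacing ATRA) will be given orally 3 times/day for 3 days prior to the chemo". SAP section 1.4 repeats both.

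Proteomics Assays Data Analysis, in the same supplement, treats the first sample as untreated: "Samples from the baseline (before treatment) and time point (after treatment) measurements formed 4 experimental subgroups". Two sets of three contrasts follow. The first set begins with "differences in protein expressions between patients with PD, SD, PR, and CR before therapy in Group A" and the second with "differences in protein expressions in pre and post therapy in Group A". Each set then has the matching Group B contrast and an A-versus-B interaction. The Figure S3 legend presents its protein list as "Proteins that differed significantly between FOLFOX4-ATRA responders and non-responders prior to treatment".

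**The concern.** ATRA is the only randomised difference between the arms, and during the 3-day lead-in only Group A takes active drug. A tube drawn on the infusion day, before FOLFOX4 starts, complies with the collection rule. In Group A it would carry 3 days of ATRA exposure, and in Group B none.

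The protocol's Introduction says that ATRA works mainly by regulating gene expression through nuclear receptors, so an early change in plasma proteins cannot be ruled out on the trial's own rationale. Two uses of the data would suffer:

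- A protein reported as separating responders from non-responders before treatment might be an early on-drug marker. It could not then be measured when treatment is chosen.
- The pre/post change in Group A would have part of the drug effect in its starting value, while the Group B change would not.

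Blinding and randomisation do not protect against this, because one calendar rule gives different drug exposure by arm. The patient random effect in the mixed model does not help either, because the problem lies in the pre value itself.

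**Working it through.** The plan states no figure to reproduce. The check sets the texts side by side.

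1. **Sampling window.** The collection rule has an upper limit (start of the first chemotherapy cycle) and no lower limit relative to study drug.

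2. **Dosing before that limit.** From Mode of Administration: 3 doses/day × 3 days = 9 doses, and 9 × 20 mg = 180 mg of ATRA in Group A. In Group B the same 9 intakes are placebo, so 0 mg.

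3. **Overlap.** A Group A sample may follow anything from 0 doses (drawn before the lead-in) to 9 doses (drawn just before FOLFOX4). Both satisfy the collection rule. The 180 mg is the most that the rule permits, not an observed exposure.

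4. **Does other text close the window?** In the text available, nothing ties the draw to the first ATRA or placebo dose, and nothing says whether the lead-in counts as part of the first cycle or of treatment. The protocol's Schedule of Events has no proteomics row, so it cannot settle the timing.

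5. **Which contrasts are exposed.** Let f be the fraction of Group A first samples drawn during the lead-in, and d the mean change in a protein that ATRA has caused in those samples. The recorded Group A baseline mean is then the true mean + f × d. The Group B baseline is unchanged.

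- Group A, response categories before therapy: for categories r and s, the difference is shifted by f_r × d_r − f_s × d_s. It is distorted if late sampling or the early effect differs between response categories.
- Group B, response categories before therapy: no shift.
- A-versus-B interaction for response: carries the Group A shift.
- Group A, post minus pre: shifted by −f × d.
- Group B, post minus pre: no shift.
- A-versus-B interaction for pre/post change: shifted by −f × d.

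So 6 − 2 = 4 contrasts are exposed. If f = 0, every shift is zero. If d has the same sign as the end-of-treatment effect, the shift pulls the pre/post contrast down. If the early change is in the opposite direction, it inflates the contrast. The documents give neither f nor d, so neither the size nor the sign can be stated.

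**The case against.** The strongest reply is that no document shows a sample taken after ATRA began. The analysis text calls the first sample a pre-treatment one. The same text and the Figure S4 legend speak of before and after FOLFOX4-ATRA, which makes ATRA part of the therapy that the pre sample precedes. A draw before the lead-in satisfies the collection rule, the analysis labels and the figure legends together.

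This stands as far as it goes. A reader might infer that the Group A baseline is not a pre-treatment sample, or that the A-versus-B interaction is biased. The documents support neither: they leave the timing open. But a label in the analysis section does not fix when the tube was drawn, and the only sentence that does set a time uses the wrong event.

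A second reply is that these are supplementary methods of a manuscript, in the past tense, with results already listed. The protocol and SAP text available contains no proteomics plan. This also stands. The absence of a proteomics row from the Schedule of Events is therefore no separate fault. The remedy also cannot be to rewrite the account of collection as though a different rule had been followed.

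Two further inferences should be resisted. All six contrasts use the first sample, but the two confined to Group B have placebo-only baselines and carry no ATRA effect. It is also tempting to put a percentage on the attenuation by assuming values for f and for the share of effect present by day 3. With nothing in the documents to bound either, such a range conveys no information, and it presumes an early effect in the same direction as the late one.

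**Conclusion.** The concern holds as a defect in the stated sampling rule. The rule permits a Group A baseline after up to 9 doses (180 mg) of ATRA, against placebo only in Group B, and the analysis then treats that sample as pre-treatment. Whether this occurred is unknown.

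If it did, four of six contrasts are exposed in the way set out above, by an amount and in a direction that the documents do not allow one to derive. The conclusion rests on reading chemotherapy as FOLFOX4, which is how Mode of Administration uses the term, and on no other text fixing the draw.

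The consequence is limited to this exploratory analysis, since OS, PFS, ORR and DCR do not use the sample. It should still be corrected, because the bias would act in one arm only and the remedy is cheap.

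**What to change.** Define the baseline proteomics sample as one drawn before the first dose of ATRA or placebo, and apply that definition in the analysis.

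For samples already collected:

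- State when they were drawn relative to the first dose, and report per arm how many fell before and after it.
- Run the pre-therapy and pre/post contrasts only on patients whose first sample preceded that dose, at least as a sensitivity analysis.
- If any sample was drawn after the first dose, qualify the protein lists that the supplement presents as differing before treatment.

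If every sample preceded the first dose, one sentence saying so closes the point. Otherwise some baselines may be lost from the exploratory analysis, with some loss of precision. The retrospective step also needs draw times and first-dose times to be recoverable, and the documents do not show that they were recorded. The change concerns sampling and analysis only and does not touch treatment.

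### The proteomics methods report no contaminant exclusion or haemolysis check, and two keratins and two red-cell proteins are among the listed proteins; handling artefact cannot be excluded for them.

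*Combined protocol and SAP*

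**What the plan says.** All of this is in the supplement's Materials and Methods and in the Figure S3 and S4 legends.

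- **Search (Protein Annotation in LC-MS/MS).** "MaxQuant search engine (v.1.6.15.0) was used to process the generated MS/MS data", and "Tandem mass spectra were compared to the human SwissProt database (20422 entries), which was concatenated with the reverse decoy database". On identification error, "FDR was adjusted to < 1" per cent. The software's contaminant settings are not given.
- **Filter (Proteomics Assays Data Analysis).** "proteins whose expression levels were undetectable in more than 40 samples were not analysed". No other protein filter is described.
- **Normalisation (same section).** "All protein expression values were normalized by calculating the relative abundance of each protein in each sample".
- **Model (same section).** The fixed effects are response category, time point and treatment group, with patient as a random effect. There is no term for site, batch or sample quality.
- **Sample handling (Collection and Storage; Extraction, Digestion, and Fractionation).** Blood is drawn into EDTA and spun, and the plasma is frozen. A later spin at 12,000 g clears debris, and the 14 most abundant proteins are depleted. No haemolysis grading is mentioned.
- **Figure S3 legend (before treatment).** CR_up contains the run "CACNA2D1, BTD, KRT81, TTR, SSC5D". RE_down contains KRT6C and the run "VCAN, SLC4A1, PLGLA".
- **Figure S4 legend (before versus after treatment).** Treat_PD_up contains the run "SLC4A1, PLS1, PFN1, PDIA3" and ends with HBG2.

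**The concern.** Keratins are common in skin and hair and can enter a sample when it is drawn or prepared. SLC4A1 (a red-cell membrane protein) and HBG2 (a haemoglobin chain) can enter plasma when red cells break. A protein that comes from the handling of the tube may say nothing about response or about ATRA.

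Three things are at stake within the proteomics work.

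1. Some listed differences may be artefacts.
2. The modules are the units of the GO and KEGG enrichment (panels B and C of both figures), so a few such entries weigh more in a short module than in the whole list.
3. Because each protein is expressed as a share of its sample, added contaminant signal lowers the share of every other protein in that tube.

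**Working it through.** There is no planned figure to reproduce. The check is whether any described step would remove these proteins, followed by a count.

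**Step 1: what each described step removes**

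| Step | What it acts on | Keratin | Red-cell protein released by lysis |
| --- | --- | --- | --- |
| Decoy search, error below 1% | False identifications | Not removed: a true keratin peptide is a correct match | Not removed |
| Detectability filter (limit of 40 samples) | Proteins seldom detected | Not removed if detected often enough | Not removed if detected often enough |
| 12,000 g spin | Debris, so possibly some membrane material such as SLC4A1 | Does not act on keratin introduced afterwards | Leaves soluble protein already released |
| Top-14 depletion | The most abundant plasma proteins | Not aimed at it | Not aimed at it |
| Mixed-model covariates | Response, time point, group | No adjustment | No adjustment |

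The lists themselves bear on the first protein column. KRT81 and KRT6C are printed as significant, so whatever the software settings were, these two keratins were not excluded before testing.

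**Step 2: count of the printed lists**

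- Figure S3: CR_up 15 + RE_down 13 + PR_up 9 + SD_down 24 + SD_up 16 = 77.
- Figure S4: Treat_RE_up 14 + Treat_RE_down 5 + Treat_SD_up 15 + Treat_SD_down 7 + Treat_PD_up 8 = 49.

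| List | Entries concerned | Share |
| --- | --- | --- |
| CR_up | KRT81 | 1/15 = 6.7% |
| RE_down | KRT6C, SLC4A1 | 2/13 = 15.4% |
| All of S3 | KRT81, KRT6C, SLC4A1 | 3/77 = 3.9% |
| Treat_PD_up | SLC4A1, HBG2 | 2/8 = 25% |
| All of S4 | SLC4A1, HBG2 | 2/49 = 4.1% |

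That is four distinct proteins in five entries. The classification is an assumption from general protein knowledge, since the documents give only gene symbols. If TPI1 and SELENBP1 in Treat_RE_up are also counted (abundant in red cells but not specific to them), S4 becomes 4/49 = 8.2%. The range for S4 is therefore 4.1% to 8.2%.

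**Step 3: effect on the other proteins**

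Let a protein have signal x in a sample whose total is T. Its share is x/T. If contaminant signal k is added, the share becomes x/(T + k), so every other protein in that tube is multiplied by T/(T + k), which is below 1. The documents give no T or k, so the size of this effect is unknown. It is the reason to remove contaminants before normalisation and not only from the final lists.

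**The case against.** The strongest case on the other side has five parts.

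1. **Not reported is not the same as not done.** This stands for the software setting and for any exclusion of haemolysed tubes, on which the text is silent. It does not stand for the two printed keratins.
2. **Artefact is not shown.** A reader might infer that the four proteins reflect sample handling and have nothing to do with response or treatment. The documents do not support that. They give no blanks, haemolysis scores, batch data or site data. Red-cell proteins may also change with disease or chemotherapy. The pattern is mixed: KRT81 is up in complete responders while KRT6C is down in responders, and HBG2 is the only haemoglobin chain listed. Since only significant proteins are printed, the absence of the others is weak evidence.
3. **A systematic bias has no clear route.** The baseline tubes were drawn before the first cycle, when response was unknown, in a blinded trial. Contamination unrelated to response adds noise. This largely stands. However, noise can still produce listed proteins: the legends give P < 0.05 without saying whether it is FDR-adjusted, the response-group sizes are not stated, and the model has no site or batch term although the protocol names three hospitals.
4. **The keratins are not treatment markers.** This stands. No keratin is in any Figure S4 module, and SLC4A1 and HBG2 are in the progressor module. The legends call the proteins significantly different and do not name them as biomarkers.
5. **The relevance is low.** Proteomics is not among the protocol's objectives or endpoints, nor among the outcomes and analyses set out in the SAP sections seen here. This stands and limits the weight of the point.

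**Conclusion.** The point holds in a limited form. The methods describe no contaminant exclusion and no haemolysis check, and the two controls that are described do neither job. Two keratins consequently remain among the baseline responder differences, and red-cell proteins appear in RE_down and Treat_PD_up. For these entries a handling artefact is a possible explanation that the analysis cannot rule out, and no more than that.

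Overall the size is small, about 4% of each figure's list (up to 8.2% in S4 on the wider classification). It is larger in single modules, at most 2 of 8 in Treat_PD_up. No effect on any particular GO or KEGG term has been shown. The conclusion rests on the outside classification of the four proteins and on the methods text being a complete account of the filters applied. It is a minor improvement to exploratory work.

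**What to change.** **Main analysis.** Remove keratins and standard contaminant entries before the relative-abundance normalisation, and state the list used and the software's contaminant setting. Then re-run the mixed models and the GO/KEGG enrichment, and re-issue the S3 and S4 modules. On the printed lists alone, this takes KRT81 from CR_up (15 to 14) and KRT6C from RE_down (13 to 12), so S3 goes from 77 to 75. Final membership may change further because the denominators change.

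**Sensitivity analysis only.** Build a per-sample red-cell index from whatever red-cell proteins were quantified, and add it to the mixed model as a covariate. Flag SLC4A1 and HBG2 as possibly lysis-related; do not delete them. State whether haemolysed samples were graded or excluded.

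**Cost.** This is a re-analysis of existing data and needs no new samples. A few proteins are lost, and the index may absorb some real disease or treatment signal, which is why it should not drive the main result.

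### The proteomics contrasts are tested with glht on lme4 fits with no stated degrees-of-freedom method; under the software default the p-values are normal-based and the nominal FDR is not assured

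*Combined protocol and SAP*

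**What the plan says.** The text is in the supplementary Materials and Methods, under Proteomics Assays Data Analysis. It sets out a chain of three steps.

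- **Model.** "Analyses of differential protein expression were conducted by fitting linear mixed models (LMM) with the lme4 R package25". The fixed effects are treatment response, "time point (pre and post treatment), and treatment group (Group A and Group B) used as fixed effects". Pairing is handled by a patient effect: "The patient ID was used as a random effect to allow us to account for the samples being paired".
- **Contrasts.** "the generalized linear hypothesis (glht) function from the multcomp R package26 was utilized to test for the following three contrasts". One set compares response categories before therapy, within each arm and between arms. A second set compares pre with post therapy in the same way.
- **Multiplicity.** "The resulting p-values were adjusted using the FDR method to account for multiple comparisons".

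The section does not say what degrees of freedom or reference distribution the contrasts used. It also omits the number of patients with proteomics data, the number per arm and response category, the number of proteins tested, and the FDR procedure, level and family. The only hints about size are a detection filter ("proteins whose expression levels were undetectable in more than 40 samples were not analysed") and the statement that all four response categories occur ("Samples from patients with PD, SD, PR, and CR were measured for each subgroup").

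**The concern.** A contrast from a mixed model is an estimate divided by an estimated standard error. Referring that ratio to a normal distribution treats the variance as known. With few patients the true tails are heavier than normal, so the p-value is too small. The relative error grows in the far tail, and that is where an FDR cut over many proteins operates.

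The FDR step takes the p-values as given and cannot correct them. If they are too small going in, a list labelled as 5% FDR can hold more false proteins than the label says. The protein lists and the enrichment analyses in Figures S3 and S4 would inherit this. It is a different question from whether the P values in those captions are raw or adjusted, because both kinds rest on the same contrasts.

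**Working it through.** The documents give no error rate, degrees of freedom or FDR level for the proteomics, so there is no stated figure to reproduce.

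**1. What the named software does.** This was checked by running it (multcomp 1.4.28, lme4 1.1.37); the documents do not cover it and do not give versions. On a simulated paired data set, glht applied to an lmer fit reported df = 0. Its p-value was 0.6358, identical to the two-sided normal tail 2Φ(−|z|). Supplying df = 22 changed it to 0.6405. The default is therefore a z-test, and a t-test is available on request.

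**2. Inputs.**
- Cells: 2 arms × 4 response categories = 8, implied by the contrasts.
- Patients n: not given. The filter can act only if there are more than 40 samples, hence at least 21 complete pairs. The upper scenario is 106, the minimum trial size in protocol section 9.1.
- Assumed: complete pairs, a model with all arm × response × time means, and intraclass correlation 0.5.

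**3. Degrees of freedom.**
- Pre/post: n within-patient differences less 8 cell means, df = n − 8. This runs from 21 − 8 = 13 to 106 − 8 = 98.
- Baseline: the variance combines the between-patient and within-patient mean squares, each on n − 8 df. At correlation 0.5 their expectations stand as 3 to 1. Satterthwaite df = (3 + 1)² / (3² + 1²) × (n − 8) = 1.6(n − 8), so about 21 to 157.

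**4. True size of a normal-based test.** Formula: 2·P(t_df > z), with z the normal critical value (1.960 for 0.05; 3.291 for 0.001).

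| n | df (pre/post) | nominal 0.05 | nominal 0.001 |
|---|---|---|---|
| 21 | 13 | 0.072 | 0.0059 (5.9×) |
| 30 | 22 | 0.063 | 0.0033 (3.3×) |
| 40 | 32 | 0.059 | 0.0024 (2.4×) |
| 60 | 52 | 0.055 | 0.0018 (1.8×) |
| 106 | 98 | 0.053 | 0.0014 (1.4×) |

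For baseline contrasts, simulated size at nominal 0.05 is 0.063 at n = 21, 0.058 at 30, 0.053 at 60 and 0.052 at 106.

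**5. Effect on FDR.** Simulation with Benjamini-Hochberg at 5% across 500 independent proteins, 10% of them carrying a true effect of four standard errors (all assumed), 400 replicates:

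| n | baseline, normal | pre/post, normal |
|---|---|---|
| 21 | 9.4% | 13.6% |
| 30 | 7.4% | 9.3% |
| 40 | 6.1% | 7.2% |
| 60 | 5.7% | 6.4% |
| 106 | 5.0% | 5.5% |

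Repeating the pre/post column with 3,000 replicates gave 13.2%, 9.3%, 7.6%, 6.3% and 5.4%, so the figures are stable to a few tenths of a percentage point.

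**6. Same simulation with a t reference.** Size at nominal 0.05 returns to about 0.05 and FDR to 4.3–4.7% at every n. The remedy works.

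**The case against.** The strongest reply is that this is silence in a short methods paragraph, not a demonstrated error. glht accepts a df argument and the authors may have supplied one. That stands. A reader might infer that the tests were certainly run without degrees of freedom, but the documents support only that none are reported and that the default gives a z-test.

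A reader might also infer that FDR control fails. The documents do not show this, because the number of paired patients is unknown. Near 106 patients, with some true signals, realised FDR is 5.0% to 5.5%. The 21-patient end is an extreme. With 42 samples the filter would keep a protein detected in only 42 − 40 = 2 of them, too few for the model described. The assumption of adjustment across proteins matters too: if the adjustment was only across contrasts within a protein, the far-tail argument loses most of its force.

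A third tempting reading blames small response groups. In this model the variance is pooled, so the degrees of freedom follow total patients minus cells. A small group mainly widens the standard error, and no group sizes are given in any case.

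A fourth is to headline the case of no true effects at all, where the chance of at least one pre/post claim at 5% FDR is about 64% at 21 patients. That takes the harshest measure, the worse contrast and the least plausible sample size together. At 106 patients the same quantity is about 10%, and for baseline contrasts about 6%.

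Finally, the captions to Figures S3 and S4 select at P below 0.05 without saying whether P is adjusted. If it is raw, the relevant error is the 7.2% to 5.3% above, which is modest. That narrows the harm but does not remove it.

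**Conclusion.** The point holds in a limited form. The method as written names software that by default gives normal-based p-values and reports no small-sample correction, so the nominal FDR is not assured. The direction is towards too many positive findings. The size runs from material (pre/post FDR about 13% at 21 patients, 9% at 30) to negligible (5.5% at 106), with baseline contrasts less affected throughout. Those figures rest on assumed patient numbers, protein count, independence, signal fraction and adjustment family. Without the number of paired patients a reader cannot tell which end applies.

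The proteomics is exploratory and is not an endpoint in the protocol or SAP sections reviewed. Nothing here bears on OS, PFS, ORR, DCR or safety.

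**What to change.** Refer each contrast to a t distribution (or F, for joint contrasts) with Satterthwaite or Kenward-Roger degrees of freedom from the same mixed model. Apply the FDR adjustment to those p-values and redraw Figures S3 and S4. If a df correction was already used, naming it is enough.

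In the same paragraph, state:
- the number of paired patients, in total and per arm and response category;
- the number of proteins tested;
- the FDR procedure, level and family;
- whether the caption P values are adjusted.

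The cost is a few lines of code and a rerun on existing data. Somewhat fewer proteins may be called significant; if the sample was large, little will change and the rerun will show it.
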